### Measures

All participants are asked to complete online measures at screening, pre-treatment, mid-treatment (4 weeks into the treatment), post-treatment (8 weeks) and at 3, 6 and 12 months post-treatment. Participants who do not complete these questionnaires are contacted via telephone and/or email to remind them to complete the measures. Participants receive a maximum of three reminders per follow-up period.

The primary outcome of the trial will be alcohol consumption in the past week as measured by Time Line Follow Back [41]. This outcome will be calculated in two ways: number of drinks in preceding week and number of heavy drinking days (defined as 4 or more drinks per day for women and 5 or more drinks per day for men) in preceding week. Secondary measures include alcohol-related problems as measured by AUDIT [35] which is a 10-item instrument. Alcohol craving will be measured by Penn Alcohol Craving Scale (PACS) [42], an instrument consisting of five items found to have both high internal consistency as well as high predictive, convergent and discriminatory validity. Alcohol-related self-efficacy will be measured by the Brief Situational Confidence Questionnaire (BSCQ) [43], consisting of eight items derived from the relapse prevention model [15]. The instrument has been found to have high both internal consistency and concurrent validity [43]. Further, the Sheehan Disability Scale (SDS) [44] adapted to alcohol’s impact on daily functioning will be used, where reliability and validity is unknown. Depression will be measured by the Patient Health Questionnaire-9 (PHQ-9) [36] and anxiety will be measured by the Generalized Anxiety Disorder-7 (GAD-7) [45], both well validated instruments. The Readiness to Change questionnaire – Treatment Version (RCQ-TV) [46] will be used at screening and at pre-treatment to assess immediate motivational changes due to the assessment interview, and to assess relation to lont-term outcomes. We will also administer the Credibility/Expectancy Questionnaire [47] at mid-treatment to assess credibility of treatment. Lastly, at post-treatment, we will administer questions pertaining to treatment evaluation and negative effects. See Table 2 for a presentation of measures included at each time point in the study.

**Table 2 Tab2:** Measures in the screening, pre-treatment, mid-treatment, post-treatment and 3, 6 and 12 month follow-ups in the Alcohol Change Course trial

Outcome Measure	Screening	Pre-Treatment	Mid-Treatment	Post-Treatment	3 Months	6 Months	1 Year
**Consent**	✓	✓					
**Alcohol consumption (TLFB)**	✓	✓	✓	✓	✓	✓	✓
**Depressive symptoms (PHQ-9)**	✓	✓	✓	✓	✓	✓	✓
**Alcohol problems (AUDIT)**	✓			✓	✓	✓	✓
**Anxiety (GAD-7)**	✓			✓	✓	✓	✓
**Alcohol craving (PACS)**	✓			✓	✓	✓	✓
**Alcohol-related self-efficacy (BSCQ)**	✓			✓	✓	✓	✓
**Readiness to change (RCQ-TV)**	✓	✓					
**Treatment Credibility& Expectancy**			✓				
**Evaluation & Negative Effects**				✓			

### Statistical analyses

The trial aims to recruit 300 participants to the four conditions (75 participants per group, see Table 3). We plan to use a multi-level hierarchical linear model with observations nested within participants when analyzing the outcome data as this method has been found superior in handling missing data in longitudinal designs. However, depending on the distribution of alcohol consumption outcomes, a multi-level hierarchical non-linear model or generalized estimating equations with an assumption of a binomial distribution may also be used. Analyses will follow the intent-to-treat principle, where all participants will be included for the outcome analysis. However, per-protocol analyses will also be conducted.

**Table 3 Tab3:** Factorial trial design and target sample per group

		Factor 1: Pre-treatment assessment interview		Total
		Yes	No	
**Factor 2: Health educator guidance**	**Yes**	75	75	150
	**No**	75	75	150
**Total**		150	150	300

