### Factor 2: health educator guidance

Participants randomized to receive health educator guidance (conditions 1 and 3) have access to health educator guidance during the eight-weeks of the course. Guides consist of social workers, counsellors and PhD psychology graduate students under supervision, with past experience delivering ICBT. The health educator’s job is to answer participant’s questions, reinforce module completion and boost motivation. All written communication between participants and health educators takes place through a secure message system on the www.onlinetherapyuser.ca website, but participants may also be contacted by phone. Phone calls are made when participants request such contact or the health educator feels a phone call would assist with client care (e.g., assess risk, address misunderstanding). When phone calls are made, health educators write a progress note on the participant’s record specifically noting the date/time of the call, and nature of contact. Health educators are spending approximately 15 min per week and participant. Health educators are blinded to whether participants have received a pre-treatment assessment interview or not.

All participants receive automated messages about the course that are sent to their regular email. These emails mainly inform the participant about any new modules accessible on the website platform. Those randomized to no guidance from a health educator (conditions 2 and 4) only receive these weekly automated email messages. They are also able to contact the OTU regarding any technical issues they experience with the site. Furthermore, a member of the research team reviews participant responses to weekly measures on alcohol consumption and depression/anxiety. Participants in conditions 2 and 4 are only contacted by the research team if the weekly measures indicate a significant clinical issue requiring attention, e.g., major increase in alcohol consumption (assessed on a case-by-case basis), a sudden increase of depression symptoms (defined as an increase of 5 in PHQ-4 since previous week) or suicidal ideation (defined as > 2 on item 9 from PHQ-9). If any participant is found to be at risk, they will be contacted and referred to appropriate health care. However, they will only be discontinued from the intervention and trial if they request it.

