### Power calculation

To estimate the sample size, we used the Factorial Power Plan provided in the R package Multiphase Optimization Strategy. Regarding effect size estimates of factor 1 (assessment interview) we had no available studies to draw on. We therefore pragmatically decided to estimate the effect size as 0.35, as this was the minimum effect size that would indicate this factor to be worth implementing considering the time spent by staff conducting the interview. Regarding effect size estimates of factor 2 (guidance), we decided to estimate it as 0.35, based on findings in previously published studies [24, 25]. Power was set at 80% and we assumed a correlation of 0.5 between pre-and post-test measurements. We also assumed an attrition of 30%. This target sample size ensures that the study is powered to detect an effect of 0.30 in unique effects of either of the two factors.

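### The outcome model names no health-educator level, so the standard error of the guidance effect will be too small if outcomes correlate within educator

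*Protocol article*

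**What the plan says.** The Statistical analyses section gives the primary model as "We plan to use a multi-level hierarchical linear model with observations nested within participants", and justifies it by its handling of missing longitudinal data. Depending on the outcome's distribution, "a multi-level hierarchical non-linear model or generalized estimating equations with an assumption of a binomial distribution may also be used". Neither the main model nor the alternatives mention the health educator.

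The section on Factor 2 describes who delivers guidance: "Guides consist of social workers, counsellors and PhD psychology graduate students under supervision, with past experience delivering ICBT". It says who receives it: "Participants randomized to receive health educator guidance (conditions 1 and 3) have access to health educator guidance during the eight-weeks of the course". For the other two conditions: "Those randomized to no guidance from a health educator (conditions 2 and 4) only receive these weekly automated email messages". On intensity: "Health educators are spending approximately 15 min per week and participant". Contact is by secure message, with phone calls on request or when the educator thinks one would help.

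On size: "The trial aims to recruit 300 participants to the four conditions (75 participants per group, see Table 3"), which makes 150 guided and 150 unguided. The Power calculation section adds: "Regarding effect size estimates of factor 2 (guidance), we decided to estimate it as 0.35". It assumes 80% power, a pre-post correlation of 0.5 and 30% attrition, and it claims power for an effect of 0.30 in either factor. It mentions no educator clustering.

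The article does not state how many educators there are, their caseloads, how participants are assigned to them, or whether a participant keeps the same educator throughout.

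**The concern.** This is a partially nested design. Guided participants belong to educators; unguided participants belong to nobody. A random effect for participant accounts for repeated measurements on one person. It does nothing for correlation between different people who share an educator.

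The article commits itself to a hierarchy, and that hierarchy leaves out a level that its own intervention creates. The guidance effect at 3 months is one of the trial's two main hypotheses, and the Discussion addresses the results to clinics and policy makers. If educators differ in how well they help their participants, the interval for guidance will be too narrow, and the power claimed for that factor will be too high.

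**Working it through.** **Inputs from the article.** 300 participants, 150 per level of guidance; 30% attrition, so 150 × 0.7 = 105 analysed per level; pre-post correlation r = 0.5; planned guidance effect 0.35; claimed detectable effect 0.30.

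**Inputs assumed.** Alpha 5% (neither alpha nor sidedness is stated); 5 to 30 educators; educator ICC from 0 to 0.10 on the baseline-adjusted outcome; equal caseloads; one educator per participant; the same total variance in both arms.

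**Step 1: the plan's own figure.** For one factor's main effect with baseline adjustment, n per level = 2(z_alpha + z_beta)²(1 − r²)/d².

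- d = 0.30, one-sided 5%: 2 × (1.645 + 0.842)² × 0.75/0.09 = 103.04, so 104 per level and 208 analysed; 208/0.7 gives 298 recruited. This matches 300.
- d = 0.30, two-sided 5%: 262 analysed, 375 recruited.
- d = 0.35, two-sided 5%: 194 analysed, 278 recruited.

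The calculation that matches 300 treats all participants as independent; it needs no educator term.

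**Step 2: effect of clustering in one arm.** With m = 105/K analysed participants for each of K educators, the guided mean has design effect 1 + (m − 1) × ICC and the unguided mean has 1. The ratio of true to model standard error for the guidance difference is therefore

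R = sqrt(1 + (m − 1) × ICC/2),

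and the true two-sided error of a nominal 5% test is 2 × [1 − Φ(1.96/R)].

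Worked case, K = 5 and ICC = 0.05: m = 21; R = sqrt(1 + 20 × 0.05/2) = sqrt(1.5) = 1.225; error = 2 × [1 − Φ(1.600)] = 11.0%. The true standard error is 22% larger than the model's; put the other way, the model's is 1 − 1/1.225 = 18% too small.

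The last column is the power for 0.35 once the true standard error is used: the unclustered standard error is sqrt(2 × 0.75/105) = 0.1195, and power = Φ(0.35/(0.1195 × R) − 1.96).

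| Educators | m | ICC | R | True error | Power for 0.35 |
|---|---|---|---|---|---|
| any | – | 0 | 1.00 | 5.0% | 83.4% |
| 30 | 3.5 | 0.05 | 1.03 | 5.7% | 81.1% |
| 15 | 7 | 0.01 | 1.01 | 5.3% | 82.3% |
| 10 | 10.5 | 0.02 | 1.05 | 6.1% | 79.9% |
| 10 | 10.5 | 0.05 | 1.11 | 7.8% | 74.9% |
| 8 | 13.1 | 0.05 | 1.14 | 8.6% | 72.7% |
| 5 | 21 | 0.05 | 1.22 | 11.0% | 66.7% |
| 5 | 21 | 0.10 | 1.41 | 16.6% | 54.4% |

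**Step 3: checks.** Simulation (4,000 trials per setting, ANCOVA ignoring educator) gave 7.1% for 10 educators and 10.7% for 5 educators at ICC 0.05, and about 5% at ICC 0. If all 150 guided participants contribute, caseloads grow and so does the error: at ICC 0.05, 9.2% with 10 educators (m = 15) and 13.6% with 5 (m = 30).

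**Step 4: which contrasts are exposed.** The guidance main effect compares conditions 1 and 3 with 2 and 4, so the educator effects stay in full. The interview main effect and the interaction involve educators only through the difference between conditions 1 and 3. An educator's shared effect cancels there if the caseload holds both conditions in equal number. The interaction is therefore exposed where caseloads are uneven across conditions 1 and 3, or where educators differ in how their effect varies with the interview. The interview main effect is exposed by the same route, with its educator part averaged with the unguided pair.

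**The case against.** The strongest reply has four parts.

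First, naming one level does not exclude another. A short article that leaves even the model family open may leave further random effects to an analysis plan. This is fair as far as it goes: a reader might infer that the plan rules out an educator level, and the text does not say so. But the article is not silent on structure; it states a hierarchy, and that hierarchy is incomplete for the design it describes.

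Second, the bias is conditional. A reader might infer that the standard errors are too small as a matter of fact. The documents do not support that: it needs a positive ICC and several participants per educator, and neither is given. There are reasons to expect a small ICC: about 15 minutes a week, mostly written messages, the same lessons for everyone, and an endpoint 3 months after treatment. The Background also reports that the guide's education did not seem to affect outcomes in ICBT for depression and anxiety, though that does not rule out differences between individual guides. All of this stands.

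Third, if guidance helps nobody, educators cannot differ in their effect, and this mechanism inflates nothing. Inflation needs educators who differ around a zero average, and an inference beyond the staff employed. An inference limited to this clinic's educators is a legitimate choice. The article does not state that choice, however, and its Discussion looks to clinics and policy makers generally. When the effect is not zero, the interval is still too narrow for that wider aim.

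Fourth, with about five educators the variance component is poorly estimated, so the remedy is weakest where the problem is largest. If participants change educator, simple nesting does not fit. Both points stand and shape the fix.

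**Conclusion.** The point holds in conditional form. The stated model has no educator level, although guidance creates one in conditions 1 and 3. Any positive within-educator correlation with shared caseloads makes the model's standard error for guidance too small. With 105 guided participants analysed, the inflation is negligible for many educators or an ICC near zero, modest for 10 educators at ICC 0.05, and material for 5 educators at ICC 0.05. All these figures rest on assumed educator numbers and ICCs, equal caseloads and one educator per participant.

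It would be too strong to conclude that the whole factorial analysis is compromised. The interview main effect is largely unaffected if both interview groups are spread evenly over educators. Randomisation of the interview, and the blinding of educators to it, make an even spread plausible, although the article does not state it. The exploratory interaction is protected by the same balance and exposed without it.

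**What to change.** - Record the educator (and any change of educator) for every participant in conditions 1 and 3, and keep the identifier in the analysis file.
- For the guidance and interaction analyses, add an educator random effect that applies only in the guided conditions (a partially nested model), with a small-sample degrees-of-freedom correction. Carry the same structure into the alternative models if they are used.
- If there are very few educators, or participants move between them, present this model as a sensitivity analysis beside the two-level one.
- Report the number of educators, their caseloads split by interview condition, and the estimated ICC.
- State in the Power calculation section that the power for guidance assumes no educator clustering.

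The cost is one variance term, one identifier and slightly wider intervals for guidance. No change to recruitment or to delivery is needed.

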### Power calculation

To estimate the sample size, we used the Factorial Power Plan provided in the R package Multiphase Optimization Strategy. Regarding effect size estimates of factor 1 (assessment interview) we had no available studies to draw on. We therefore pragmatically decided to estimate the effect size as 0.35, as this was the minimum effect size that would indicate this factor to be worth implementing considering the time spent by staff conducting the interview. Regarding effect size estimates of factor 2 (guidance), we decided to estimate it as 0.35, based on findings in previously published studies [24, 25]. Power was set at 80% and we assumed a correlation of 0.5 between pre-and post-test measurements. We also assumed an attrition of 30%. This target sample size ensures that the study is powered to detect an effect of 0.30 in unique effects of either of the two factors.

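### The power section plans on an effect of 0.35 but claims power for 0.30; at two-sided 5% with baseline adjustment and 30% attrition, 300 participants give about 70% power at 0.30 and 80% only from about 0.34

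*Protocol article*

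**What the plan says.** All of the inputs are in the protocol article, under Statistical analyses and Power calculation.

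- **Size:** "The trial aims to recruit 300 participants to the four conditions (75 participants per group, see Table 3"). Table 3 gives 150 against 150 for each main effect.
- **Factor 1 (interview):** no earlier studies were available. "We therefore pragmatically decided to estimate the effect size as 0.35", described as the smallest effect that would justify the staff time.
- **Factor 2 (guidance):** "we decided to estimate it as 0.35, based on findings in previously published studies".
- **Other inputs:** "Power was set at 80"%, a pre-post correlation of 0.5, and "We also assumed an attrition of 30"%.
- **Conclusion:** the target of 300 "ensures that the study is powered to detect an effect of 0.30 in unique effects of either of the two factors".

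The section does not say why the figure moves from 0.35 to 0.30. It gives no significance level or sidedness, and does not say whether the correlation entered through a covariate or a change score. Statistical analyses adds that every participant enters an intention-to-treat multilevel model.

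**The concern.** The closing sentence asserts a design property, and a reader can test it against the inputs given just before it. At the usual two-sided 5% it fails once the stated attrition is applied.

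Readers will use that sentence to judge how sensitive the trial was if a main effect turns out not to be significant. They would credit it with 80% power at 0.30, when about 70% is the better figure, or about 58% if the analysis does not adjust for baseline. The second case cannot be ruled out, because the article names a multilevel model without saying how baseline enters. In that case even the planned 0.35 falls short of 80%.

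**Working it through.** **Inputs from the article.** 300 randomised, 150 per factor level; attrition 30%; correlation r = 0.5; power 80%; effects 0.35 (planned) and 0.30 (claimed).

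**Assumptions, not in the article.** Two-sided 5% as base case, with two-sided 10% (the same as one-sided 5%) as the lenient alternative. Effects are in units of the outcome SD. Each main effect compares two halves of a balanced factorial.

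**Participants with 3-month data.** 300 × 0.7 = 210, or 105 per factor level.

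**Residual SD, s.** Baseline as covariate: s = √(1 − 0.5²) = 0.866. Change score: s = √(2(1 − 0.5)) = 1. No baseline adjustment: s = 1.

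**Standard error of a main effect.** s × √(4/N). With N = 210 and s = 0.866 this is 0.866 × 0.138 = 0.1195; with s = 1 it is 0.138.

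**Step 1: try to reproduce the claim.** Required N = 4s²(z for alpha + z for power)²/d², rounded up per factor level, then divided by 0.7.
- Two-sided 5%, covariate, d = 0.30: 4 × 0.75 × (1.960 + 0.842)²/0.09 gives 262 with data, so 375 recruited. The target of 300 is not reproduced.
- Two-sided 10%, covariate, d = 0.30: 4 × 0.75 × (1.645 + 0.842)²/0.09 gives 208 with data, so 298 recruited. This does reproduce 300.

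**Step 2: what 300 gives in the base case.** The noncentrality is 0.30/0.1195 = 2.51 at 0.30 and 0.35/0.1195 = 2.93 at 0.35. The noncentral t gives power of 70.5% and 83.0%. The smallest effect with 80% power is 2.802 × 0.1195 = 0.335 (0.336 by noncentral t).

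**Step 3: range over the unstated choices.** Power is by noncentral t; the other columns use the normal approximation.

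| Model and level | Power at 0.30 | Power at 0.35 | Smallest effect at 80% power | Recruits for 0.30 / 0.35 |
|---|---|---|---|---|
| Covariate, two-sided 5% | 70.5% | 83.0% | 0.335 | 375 / 278 |
| Change score or unadjusted, two-sided 5% | 58.1% | 71.4% | 0.387 | 501 / 369 |
| Covariate, two-sided 10% or one-sided 5% | 80.4% | 89.9% | 0.297 | 298 / 218 |
| Change score or unadjusted, two-sided 10% or one-sided 5% | 69.9% | 81.1% | 0.343 | 395 / 289 |

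If attrition cost no information (N = 300, covariate, two-sided 5%), the standard error is 0.866 × √(4/300) = 0.100. Power at 0.30 is then 84.9%, and the smallest effect with 80% power is 0.280.

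**Step 4: which reading fits the target of 300.** The one row that supports 0.30 makes 300 generous for 0.35, which would need only 218. The base case needs 278 for 0.35 (280 by noncentral t), which sits naturally with 300. The last row needs 289 for 0.35, also close to 300, but does not support 0.30. In no row does 300 correspond to both effects.

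**The case against.** Four points can fairly be made for the article.

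1. **The 70% does not follow from attrition and correlation alone.** It also needs an alpha, a sidedness and a pretest model, and one admissible set (covariate, one-sided 5% or two-sided 10%) gives 298 recruits for 0.30. The hypotheses under Purpose and aims are directional. This stands: the assumptions must be labelled and the range shown. It does not rescue the sentence, because the supporting choice is undisclosed and fits poorly with planning on 0.35.

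2. **210 is not the analysis set.** All participants enter the multilevel model, and Table 2 schedules alcohol consumption at seven time points, so those lost by 3 months still contribute earlier data. This also stands, and the correction should speak of participants providing 3-month data. How much information is recovered is unknown. In the covariate case at two-sided 5%, the limits are 70.5% (none) and 84.9% (all). Reaching 80% at 0.30 needs about 264 participants' worth of data by noncentral t, so about 264 − 210 = 54 of the 90 lost would have to be made good. The article gives no basis for assuming that.

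3. **0.35 and 0.30 need not conflict.** A reader might infer a contradiction about the trial's target. The text does not support that: planning on one effect while having power for a smaller one is coherent, provided the second claim is true. The two could even be one effect on two scales, since 0.30/0.866 = 0.346. The article does not say so, and power at 0.30 outcome SDs would still be about 70%.

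4. **An article may leave alpha and the pretest model to the full protocol or analysis plan.** Agreed; their absence is not the fault here. The fault is a positive claim of power that the inputs given do not support at the conventional level.

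**Conclusion.** The point holds in a limited form. The claim of power for 0.30 is unexplained and cannot be reproduced at two-sided 5% once the article's 30% attrition is counted. With baseline as a covariate, 300 randomised and about 210 providing 3-month data, power is about 70% at 0.30 and 83% at 0.35, and 80% is reached from about 0.34. Over the unstated choices, power at 0.30 runs from about 58% to about 80%.

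A reader might go further and conclude that the trial is too small. The figures do not show that: under baseline adjustment 300 exceeds the roughly 280 needed for the planned 0.35, which is also the smallest effect that the article considers worthwhile for the interview. Nor does the power figure settle what a non-significant result would exclude; the confidence interval does that.

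The sufficiency for 0.35 does depend on baseline adjustment. At two-sided 5% without it, power at 0.35 is about 71%.

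**What to change.** Keep the target of 300. State the alpha, the sidedness and the pretest model used in the calculation, and replace the closing sentence with the figure that these inputs support. At two-sided 5% with baseline adjustment it would read:

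> With 300 randomised and about 210 participants assumed to provide 3-month data, a two-sided 5% test of each main effect, adjusted for screening consumption (r = 0.5), has about 83% power for an effect of 0.35. The smallest effect detectable with 80% power is about 0.34; power for 0.30 is about 70%.

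If the calculation in fact used one-sided 5% or two-sided 10%, say so and report power at 0.30 as about 80% at that level.

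Specify that the 3-month main-effect contrasts are adjusted for consumption at screening. The screening value is the right baseline because the pre-treatment measure follows randomisation and the interview, so adjusting for it could absorb part of the interview's effect.

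The cost is one rewritten sentence, one added specification, and a stated detectable effect slightly less favourable than 0.30. Recruitment, randomisation and endpoint are untouched.
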